**Evaluation of efficacy of two different preventive therapy regimens for tuberculosis in HIV infected persons**

## INTRODUCTION

##### HIV and Tuberculosis

The HIV infection has increased the burden of TB, especially in populations where the prevalence of TB infection is high among young adults. India has the largest number of HIV-infected people, largest number of tuberculosis cases and also the largest number of dually infected individuals, in the world. Infection with HIV is the most potent known risk factor for progression to active tuberculosis among adults.

Tuberculosis hastens the development of AIDS in HIV-infected persons. Individuals who are not HIV-infected and who become infected with *Mycobacterium tuberculosis* have an approximately 10 percent lifetime risk of developing active tuberculosis, compared with a risk of 60 percent or more in persons infected with HIV*.* This is particularly important in India where it is estimated that more than half of the adult population harbors *M.tuberculosis.*

Current estimates indicate that TB is by far the commonest opportunistic infection occurring among HIV positive persons in India and that 60 to 70% of HIV positive patients will develop tuberculosis in their lifetime. Several studies from different parts of the country have also documented high HIV sero-prevalence rates among tuberculosis patients. In a developing country like India, the potential extra burden of new tuberculosis cases attributable to HIV could overwhelm the already stretched tuberculosis budgets and support services.

Despite their increased susceptibility to TB, patients with HIV/AIDS can be cured of TB by Directly Observed Therapy, Short-Course (DOTS). DOTS is a technical and management package aimed at diagnosing and curing as many infectious tuberculosis cases as possible with the twin goals of >85% cure rate and 70% case-finding. If effectively implemented, this strategy should cut the chain of transmission in the community by curing most of the infectious cases. The Revised National Tuberculosis Control Program (RNTCP) utilizes the five components of DOTS and is being implemented in India in a phased manner from 1993 onwards.To date, a population of 250 million has been covered and the entire country is expected to be covered by 2004. Recognizing the serious threat posed by TB/ HIV co-infection, the RNTCP calls for strengthening collaboration between TB and AIDS control programs for better management of HIV-infected patients with TB. However, to date, there are no specific technical guidelines for diagnosis, treatment or prevention of TB among HIV infected persons.

Diagnosis of tuberculosis among HIV-infected persons is often delayed and difficult to make, as HIV-infected persons with TB are more likely to have negative sputum smears and minor and non-specific x-ray abnormalities. Among HIV-infected persons with an intact immune system, the clinical presentation is similar to that among HIV negative individuals. However, the pathogenesis and clinical features of TB change markedly among HIV positive persons with immunodeficiency (e.g CD4 counts of < 200). Studies comparing the proportion of sputum smear positive patients among HIV infected and non-infected tuberculosis patients have found a lower proportion of sputum smear positive patients among those with HIV infection compared with HIV negative patients. Recently, a diagnostic algorithm using the response to a course of broad - spectrum antibiotics has been used in an attempt to improve the specificity of diagnosis of smear-negative tuberculosis and this approach has been incorporated into the RNTCP also.

Among HIV-infected persons there is a prime need for early and accurate detection of smear positive TB to prevent further spread in the community, and there is also a need to accurately diagnose and treat smear-negative cases not only for individual health benefits but also to reduce the number of smear-positive cases that arise in future. It is unknown whether the current diagnostic criteria and investigations recommended by the RNTCP are adequate to effectively diagnose tuberculosis in HIV positive persons. Specifically, the use of less stringent or broader symptom complex for screening and the yield from 3 additional sputum specimens for AFB smear and mycobacterial culture needs investigation.

Although optimal treatment of TB among HIV-infected persons is crucial, current knowledge and recommendations for duration of treatment in this group of patients are equivocal. In the past decade several studies have examined the effectiveness of treatment of TB among HIV-infected persons (Annex 1). A study has also suggested that post-treatment maintenance therapy with a combination of Isoniazid and Sulfadoxine-Pyrimethamine significantly reduces recurrence rates and decreases mortality following short-course chemotherapy. Recently the effect of Trimethoprim-Sulfamethoxazole (Co-trimoxazole) in significantly decreasing mortality and hospital admission rates in HIV-infected patients with tuberculosis has also been demonstrated.

In India, the Revised National Tuberculosis Control Program (RNTCP) is being introduced in a phased manner and it is expected that all tuberculosis patients will be treated with intermittent short-course regimens using the DOTS strategy.Under the RNTCP, HIV/TB patients are currently being treated with the standard regimens, but the effectiveness of these regimens among TB patients with HIV infection is unknown.

Preventive therapy (PT) against TB is the use of one or more anti-tuberculosis drugs given to patients with latent infection with *Mycobacterium tuberculosis* in order to prevent the progression to active disease. HIV is the major cause of the large increase over the last decade in the incidence of tuberculosis in populations with a high prevalence of HIV infection. Several studies have now demonstrated that PT is effective in preventing TB in individuals dually infected with HIV and *M. tuberculosis*. Studies conducted in USA, Africa and Haiti indicate that preventive therapy is efficacious in HIV positive persons with tuberculin reactions > 5mm, and that the optimal duration of isoniazid preventive therapy (using a single drug) should be greater than six months to provide the maximum degree of protection. Recently, a two-month regimen of daily rifampicin and pyrazinamide was found to provide protection equivalent to daily isoniazid for one year. The advantage of shorter regimens is better patient compliance and possibly earlier sterilization of lesions; however, the risk of drug toxicity maybe higher. The efficacy of preventive therapy in Mantoux negative HIV+ persons has not been clearly established, most studies showing it to be of limited value. Results of prevention trials conducted around the world are summarized in Annex 2.

Although there is large body of literature indicating benefit from preventive therapy, particularly among Mantoux Test (MT) positive persons, several issues regarding preventive therapy for tuberculosis in HIV positive persons need to be addressed in the endemic Indian setting. Due to the continuous environmental exposure to mycobacteria in the Indian setting, it is likely that HIV positive persons are at increased risk for disease due to both re-activation and re-infection. Hence, HIV positive persons who are Mantoux negative could also be at a high risk for developing tuberculosis following primary infection. In this setting, there is need to evaluate the efficacy of prophylaxis for tuberculosis in both tuberculin positive and negative individuals. The duration of preventive therapy required in an endemic setting is another areas requiring further investigation. Currently, preventive therapy is not included as part of the RNTCP. However, the growing problem of HIV in India could make prevention of tuberculosis in this high-risk group a priority area in the years to come.

**Purpose of the proposed study**

The HIV epidemic has a major impact on the epidemiologic dynamics of tuberculosis and poses several challenges to control of TB in a resource-poor country like India. HIV/TB burden can be brought under control by interventions that reduce the risk of progression of TB infection to overt disease (by preventive therapy), by timely diagnosis of TB among HIV-infected by cases finding using enhanced diagnostic criteria, and by adequate and effective treatment. Given the serious threat posed by the HIV epidemic on control of TB, and the current gaps in knowledge related to diagnosis, prevention and treatment of TB among HIV-infected persons in the Indian population, it is proposed to conduct a randomized control clinical study with the following interrelated objectives.

**Study Objective**

To compare the efficacy of two TB preventive therapy regimens in reducing the incidence of tuberculosis and mortality among HIV-infected persons.

**Study Design**

The study will be a two-armed prospective randomized clinical trial among HIV- positive patients without active tuberculosis. Enrolled patients will be assigned to one of the two unsupervised self-administered treatment regimens i.e. EH for 6 months or INH alone for 3 years. At the end of a 3-year follow-up, incidence of TB and overall mortality will be compared in each group.

**Study population and enrollment**

All HIV positive patients seeking care at one of the study centers, above the age of 15 years, not suffering from a serious illness, non-pregnant, and in whom TB was ruled out using the enhanced screening process described in section I, will be approached to participate in the study. The consent form for prophylaxis trial will be read to the patients in the local language and written consent will be obtained from willing patients.

**Enrollment and baseline investigations**

All patients who provide a written consent to participate in the trial will be interviewed by a social worker using a standard questionnaire. Patients with previous history of TB treatment of greater than 1 month or those on anti-retroviral drugs will be excluded from the study. Blood samples will be collected from patients meeting initial eligibility criteria to test for laboratory eligibility criteria. Standardized laboratory investigations will include complete heamogram (total and differential leucocyte counts, platelet counts and haemoglobin estimation), Renal function test (serum uric acid, blood urea, serum creatinine), Liver function tests, random blood sugar (BS), urine albumin and urine sugar. Patients who fulfill laboratory criteria (hemoglobin =>70 g/L, granulocyte count >1.1 X 109/L, platelet count > 100X 109/L, serum alanine amino transferase concentration <2.5 times the upper limit of normal, and serum creatinine concentration <1.1 mg%, random blood sugar < 140 mg%) will be enrolled in to the study.

Patients whose CD4+ cell count is below 100 absolute count or 10% of the total leucocyte count will not be admitted to the study, as they may have a latent focus of tuberculosis, which cannot be diagnosed by standard techniques available.

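### The two limits of the CD4 exclusion conflict: for every laboratory-eligible patient, 10% of total leucocytes exceeds 100 cells/µL, so the 100-cell limit is redundant as written

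*Protocol*

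**What the plan says.** The protocol's section on enrollment and baseline investigations sets the CD4 rule in one sentence: "Patients whose CD4+ cell count is below 100 absolute count or 10% of the total leucocyte count will not be admitted to the study". The reason given is that such patients are kept out "as they may have a latent focus of tuberculosis, which cannot be diagnosed by standard techniques available". No unit is attached to the 100.

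The paragraph before it lists the laboratory entry criteria, among them "granulocyte count >1.1 X 109/L" (the exponent was flattened when the text was extracted; the value is 1.1 × 10⁹/L). The baseline haemogram includes "total and differential leucocyte counts, platelet counts and haemoglobin estimation", so the denominator named in the CD4 rule is available at screening and a centre can apply the rule as worded.

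No other section restates, explains or corrects the percentage or its denominator. The protocol gives no expected distribution of leucocyte or CD4 counts.

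**The concern.** The sentence sets an absolute count beside a percentage as if both marked roughly the same level of immune depletion. With total leucocytes as the denominator they do not. The granulocyte criterion puts a floor under the leucocyte count, and that floor is already high enough for the percentage to overtake the absolute limit in every patient who meets it.

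What is at stake is the definition of the trial population. The study section on population and enrollment refers to several study centers. A centre that applies the sentence literally, one that treats 100 cells as the operative limit, and one that assumes another denominator would each admit different patients. Randomization balances the arms within whoever is admitted, but it cannot settle which population the result describes.

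**Working it through.** **Inputs.** All come from the section on enrollment and baseline investigations, except where marked as assumed.
- Absolute limit: 100, unit not stated, taken as cells/µL.
- Percentage limit: 10% of the total leucocyte count (WBC).
- Granulocytes > 1.1 × 10⁹/L = 1,100/µL.
- WBC values used for illustration: assumed.

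**Step 1. Where the two limits agree.** 0.10 × WBC = 100 gives WBC = 100 / 0.10 = 1,000/µL.

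**Step 2. Whether an eligible patient can be there.** Granulocytes are a subset of leucocytes, so WBC ≥ granulocytes > 1,100/µL. The 10% limit is therefore above 0.10 × 1,100 = 110/µL. The point of agreement is out of reach.

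**Step 3. Lowest CD4 count that can pass the percentage limit.** CD4 cells are leucocytes too, and are not granulocytes, so WBC ≥ granulocytes + CD4. Passing requires

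CD4 ≥ 0.10 × WBC > 0.10 × (1,100 + CD4),

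hence 0.90 × CD4 > 110 and CD4 > 110 / 0.90 = 122/µL. Nobody at or below 122/µL can be admitted under the percentage limit, so the 100-cell limit excludes no one further.

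**Step 4. The rule under each reading.**

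| Reading of the sentence | Effective rule among laboratory-eligible patients |
| --- | --- |
| Either limit excludes (literal) | Cut-off = max(100, 0.10 × WBC) = 0.10 × WBC; the absolute limit is redundant |
| Both limits must be met to exclude | Cut-off = 100; the percentage limit is redundant |
| Two alternative measures of one threshold | Cut-off is 100 or 0.10 × WBC according to which is used; the two are never equal |

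The readings give different decisions for any patient whose CD4 count is at least 100 but below 10% of WBC.

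**Step 5. Size of the gap under the literal reading.**

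| WBC (/µL) | 10% of WBC (/µL) | Ratio to 100 |
| --- | --- | --- |
| 1,100 (eligibility floor) | 110 | 1.1 |
| 2,000 (assumed) | 200 | 2 |
| 4,000 (assumed) | 400 | 4 |
| 6,000 (assumed) | 600 | 6 |
| 8,000 (assumed) | 800 | 8 |

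Only the first row comes from the protocol.

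**Step 6. Whether lymphocytes as denominator would align the limits.** 10% of lymphocytes equals 100 only at 1,000 lymphocytes/µL. If lymphocytes are assumed to be 20–40% of leucocytes, 10% of lymphocytes is 80–160/µL at WBC 4,000, 120–240 at 6,000 and 200–400 at 10,000. The limits come closer but still do not select the same patients.

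**The case against.** The strongest reply is that this is a wording slip, probably leucocyte for lymphocyte, which clinic staff would recognise. Nothing shows that centres differ in how they read it, and eligibility is settled before randomization and equally for both arms. On that view a clarification is enough. Much of this stands. The comparison between arms is not biased under any reading, and divergence between centres is a risk, not something the document shows. But the document cannot confirm the slip, and the sentence can be applied literally with counts taken at screening.

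A second reply is that the 100-cell limit does act if the limits are alternatives, with whichever is available being used. That is correct, so redundancy belongs to the literal reading. Under the alternative reading the defect is that the two measures never agree.

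A reader might also infer more than the protocol supports:
- **Patients several times above 100 are turned away in large numbers.** The multiple depends on leucocyte counts the protocol does not give. The only bounds it yields itself are 110 and 122/µL, about 1.1 to 1.2 times the stated limit.
- **Tuberculosis incidence would fall below the planned 7/100 person-years, and power with it.** The protocol gives no incidence by CD4 level and does not describe the CD4 mix behind the 7/100, so this cannot be derived.
- **The rule contradicts the Introduction.** Its mention of "CD4 counts of < 200" is a background example about how the clinical picture of tuberculosis changes. It sets no entry limit, and the 100 in the rule already differs from it. A higher cut-off may reach further than the stated reason needs, but it does not contradict that reason.

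**Conclusion.** The CD4 exclusion is wrong as written. Taken literally, its absolute limit is redundant for every patient who meets the granulocyte criterion, and the operative rule is a CD4 count of at least 10% of all white cells, always above 110/µL. Taken as two measures of one threshold, the limits disagree for every laboratory-eligible patient. On either reading the sentence does not fix one population.

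This rests on the protocol's own figures and one assumption, that the 100 is in cells/µL. The size of the discrepancy beyond the eligibility floor rests on assumed leucocyte counts: 2-fold at 2,000/µL, 4-fold at 4,000/µL and 6-fold at 6,000/µL. A slip for lymphocytes is plausible but unproven, and substituting that word alone would not make the two limits equivalent. No conclusion about incidence, power or bias between arms follows.

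**What to change.** Before enrolment, the sponsor should amend the CD4 sentence in the section on enrollment and baseline investigations so that the two limits are reconciled. The amended text should state:
- the denominator intended for the percentage;
- the unit of the absolute count;
- how the limits combine: either one excludes, both are needed, or one replaces the other when it is unavailable.

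That single definition should go to all centres, preferably with one worked example. The choice of cut-off is the sponsor's, and none is proposed here.

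The cost is a short eligibility amendment. Total and differential leucocyte counts and CD4 are already measured at baseline, so no new test is needed. Once patients have been admitted under differing readings, the enrolled population cannot be redefined.

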**Sample Size**

Assuming that prophylaxis will result in reduction of the incidence of TB in HIV positive persons from 7/100 person years (published TRC study) to 3/100 person years, the sample size for each arm is calculated to be 250. Allowing for a 10% drop out rate per year due to death or default, the number of patients required per treatment arm will be 325.

Total number of patients to be admitted to the study: 650

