# The treatment regimens in each study group will be as follows:

1. Ethambutol (800 mg) and Isoniazid (300 mg) daily for six months, self-administered, collected once in fifteen days.
2. Isoniazid (300 mg) daily for 3 years (in lieu of lifelong prophylaxis) with fortnightly collection of drugs

Subjects in both study groups will receive 10 mg of Pyridoxine daily during treatment.

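### The sample size rests on the effect of prophylaxis itself (7 to 3 per 100 person-years), but both arms receive prophylaxis and no expected difference between the regimens is given

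*Protocol*

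**What the plan says.** The Sample Size section opens with "Assuming that prophylaxis will result in reduction of the incidence of TB in HIV positive persons from 7/100 person years (published TRC study") and continues "to 3/100 person years, the sample size for each arm is calculated to be 250". It then adds "Allowing for a 10% drop out rate per year due to death or default, the number of patients required per treatment arm will be 325", for a total of 650.

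The comparison is described elsewhere. The Study Objective is "To compare the efficacy of two TB preventive therapy regimens". Under Study Design, patients are assigned to "EH for 6 months or INH alone for 3 years". The list of regimens gives the first arm as "Ethambutol (800 mg) and Isoniazid (300 mg) daily for six months" and the second as isoniazid, also 300 mg daily, for three years. The section on statistical analysis and outcome measures names development of tuberculosis as the primary endpoint and compares the two groups by log-rank test. No section gives an expected rate for either regimen, an expected difference between them, or a margin.

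**The concern.** The fall from 7 to 3 is attributed to prophylaxis, and every randomised patient receives prophylaxis. Read literally, the calculation sizes a trial of prophylaxis against nothing. The contrast between two active regimens is normally smaller. Here it is probably smaller still in the first six months, when both arms take the same daily isoniazid dose and differ only by ethambutol.

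The Sample Size section is the only place where the protocol says what difference the primary comparison is built to detect. If that difference belongs to another comparison, a reader cannot tell what a significant or a non-significant log-rank result would mean.

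**Working it through.** **Inputs from the protocol.** Rates of 7 and 3 per 100 person-years; 250 per arm; 325 per arm enrolled; 10% loss per year; three years of follow-up from admission; equal allocation; log-rank test.

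**Assumptions.** Two-sided 5%, because alpha and power are not stated in the protocol. The regimen-specific rates are also assumed and are shown as a range.

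**1. The plan's own figure.** Three-year risks are 1 − exp(−0.21) = 0.189 and 1 − exp(−0.09) = 0.086. The two-proportion formula at 90% power gives 232 per arm, or 251 with continuity correction. Other choices for the same rates also land near 250: Freedman's formula at 80% power, two years and simple rates needs 50 events in all, and 50/(0.14 + 0.06) = 250. So 250 is compatible with 7 vs 3, but the route cannot be identified. At 250 evaluable per arm, 7 vs 3 has about 92% power (two proportions) or 94% (Schoenfeld). The figure 325 is 250 × 1.30.

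**2. Rates differing from day 0.** With h = −ln 0.9 = 0.1054, expected events per arm are 325 × r/(r + h) × (1 − exp(−3(r + h))). Power is Φ(√(D/4) × |ln RR| − 1.96), where D is total events and RR the rate ratio.

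- 7 vs 3: D = 53.1 + 24.0 = 77.1; √(77.1/4) × 0.847 = 3.72; 3.72 − 1.96 = 1.76; power 96%.
- 5 vs 3: D = 39.0 + 24.0 = 63.0; √(63.0/4) × 0.511 = 2.03; 2.03 − 1.96 = 0.07; power 53%.

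**3. No difference in months 0 to 6.** Both arms run at 3/100 until month 6 and diverge afterwards. These powers come from simulated log-rank tests (at least 4,000 trials per case). A hand check for 5 vs 3:

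- Early events: 325 × 0.03/0.1354 × (1 − exp(−0.0677)) = 4.7 per arm, 9.4 in all.
- Still at risk at month 6: 325 × exp(−0.0677) = 303.7 per arm.
- Later events: 31.5 (EH) and 19.3 (INH), 50.8 in all; total 60.2.
- Only the later events carry the contrast: (50.8 × 0.511/4)/√(60.2/4) = 6.49/3.88 = 1.67; 1.67 − 1.96 = −0.29; power about 39%, which agrees with the simulation.

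| EH rate per 100 PY (INH at 3) | Power, differing from day 0 | Power, no difference in months 0–6 |
|---|---|---|
| 7 | 96% | 84–86% |
| 6 | 83% | about 65% |
| 5 | 53% | about 38% |
| 4 | 19% | about 13% |
| EH rate needed for 80% | about 5.9 | about 6.7–6.8 |

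On the scale of the assumed benefit (7 − 3 = 4), 5.9 means that EH keeps (7 − 5.9)/4, about a quarter. In the last column, 6.7 to 6.8 means that EH keeps (7 − 6.8)/4 = 5% to (7 − 6.7)/4 = 8% of it after month 6.

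**4. A lower INH rate.** Differing from day 0, with INH at 2/100: 5 vs 2 gives 93%, 4.5 vs 2 gives 83%, 4 vs 2 gives 67% and 3.5 vs 2 gives 46%.

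**5. Equal rates.** If both arms run at 3/100 throughout, D = 48.1. The 95% interval around a hazard ratio of 1 is exp(±1.96 × 2/√48.1), about 0.57 to 1.76.

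**The case against.** The best defence is that a large difference is a plausible design hypothesis. The Introduction says that isoniazid needs more than six months for its fullest protection and that continuing exposure in India adds re-infection to re-activation. The regimen list presents three years of isoniazid as a substitute for lifelong treatment. EH patients are off drug for 30 of 36 months. If EH protects fully while taken and the rate then returns to 7/100, power is still about 84 to 86%. A stronger INH effect would also restore power, as 5 vs 2 shows.

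This stands, and it limits the point. A reader might infer that the design lacks power. The documents do not support that, because power depends on regimen rates that they nowhere give. Nor do they support saying that EH would have to be useless from day 0 for the size to suffice, or that 250 is an arithmetic error or can be obtained in only one way.

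A reader might also infer that a null result would be reported as equal efficacy. The protocol does not say so, and rules for reporting a non-significant result commonly belong to the SAP, which is not at hand.

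The defence does not supply the missing step. The Sample Size section credits the fall to prophylaxis in general. It does not say that 7/100 is the rate expected under EH, or in which months.

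**Conclusion.** The point holds as a fault in the stated basis of the sample size. The size of 250 (325) per arm is derived from a contrast that the trial does not test, and nothing is stated for the contrast that it does test. The number is adequate if the regimens differ about as much as prophylaxis and none, or by a similarly large ratio at lower rates. For moderate differences it is not: with INH at 3/100 and EH at 5/100, power is about 53% if the rates differ from day 0 and about 38% if they differ only after month 6. All these powers rest on the assumed two-sided 5% level, 10% yearly loss, three years and the assumed regimen rates. The wording should be corrected because it governs how the primary comparison is read.

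**What to change.** Keep 650 patients. In the Sample Size section, replace the present justification with the TB rate expected under each regimen, the reason for each, the alpha with its sidedness, and the power for that contrast. Say whether a difference is expected in months 0 to 6.

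Then state what 325 per arm delivers on that one set of assumptions. The two sets must not be mixed: with no difference in months 0 to 6, 80% power against INH at 3/100 needs EH at about 6.7 to 6.8/100, whereas 5.9/100 applies only if the rates differ from day 0. Show the range over the INH rate as well as the EH rate.

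The cost is protocol wording only, with no extra patients and no change to treatment or follow-up. The drawback is that the stated power will probably look less favourable than the present text implies.

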**Follow-up**

During chemoprophylaxis

All enrolled patients will be followed up regularly to monitor general clinical status, adverse effects, adherence to drugs and development of active tuberculosis. Patients will be called to the clinic three monthly for a thorough clinical assessment and measurement of weight (see table). During each clinic visit, patients will be verbally screened for chest symptoms. In the presence of chest symptoms, the patient will be thoroughly evaluated clinically, and investigated for tuberculosis by radiological examination and 3 sputum specimens for smear and culture.

During each follow up visit the patient will asked for any symptoms or signs of drug toxicity. Details of any adverse reactions and their management will be recorded on a standardized toxicity form. Adverse reactions will be appropriately managed.

Adherence to the assigned regimen will be checked by detailed questioning of patients, return of empty drug packs, and by examination of spot urine samples for acetyl isoniazid. Non-adherent patients will be counseled regarding importance of treatment regularity and monitored closely. If a patient fails to attend the on the due date for drug collection, a letter will be posted, following which a health visitor or social worker will visit his/her home in case there is no response within a week.

Post Chemoprophylaxis

Patients will be followed up for a period of three years from the time of admission to the study. Clinical examination and relevant investigations will be done 3 monthly. Patients suspected to have tuberculosis at any time will be fully investigated and treated appropriately. Any positive culture will be subjected to drug susceptibility tests. If a patient dies, a verbal autopsy will be conducted to ascertain the cause of death**.**

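### The drop-out allowance is wrong as written: 325 per arm does not leave 250 after three years of 10% annual loss, although the effect is small

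*Protocol*

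**What the plan says.** The Sample Size section assumes that TB incidence falls "from 7/100 person years (published TRC study) to 3/100 person years" and states that "the sample size for each arm is calculated to be 250". It then allows for a "10% drop out rate per year due to death or default, the number of patients required per treatment arm will be 325". The enrolment target follows: "Total number of patients to be admitted to the study: 650". No inflation formula is given, and the section does not say whether 250 counts patients who complete follow-up or stands for an amount of person-time.

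The Follow-up section fixes the horizon: "Patients will be followed up for a period of three years from the time of admission to the study". The section on statistical analysis and outcome measures plans to estimate TB incidence per person-year and to compare the arms by the log-rank test, on an intention-to-treat basis.

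**The concern.** An allowance for loss should divide the number needed by the fraction expected to remain. Here the result matches multiplication by one plus the total loss, which always gives a smaller number. A reader of the Sample Size section would take it that 250 per arm remain after the stated loss, and at the stated rate and duration they do not. The target of 650 rests on this one step, so the step should follow from its own inputs. What is at stake is the soundness of the stated justification, more than the adequacy of the trial.

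**Working it through.** **Inputs.** From Sample Size: 250 per arm before loss, 10% loss per year, 325 per arm after the allowance, 650 in total, TB rates of 7 and 3 per 100 person-years (taken here as the rates in the two arms). From Follow-up: three years per patient.

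**The plan's figure.** 250 x (1 + 3 x 0.10) = 250 x 1.30 = 325, an exact match, and 2 x 325 = 650.

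**Number needed to retain 250 at 36 months.**
- 10% of those remaining lost each year: 250 / 0.9^3 = 250 / 0.729 = 342.9, so 343 per arm (686 in total).
- 10% of the original number lost each year: 250 / 0.70 = 357.1, so 358 per arm (716 in total).

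**Number that 325 leaves.**
- 325 x 0.729 = 236.9, about 237 (13 short, 5%).
- 325 x 0.70 = 227.5, about 228 (22 short, 9%).

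For 325 to leave 250, the total three-year loss would have to be 1 - 250/325 = 23.1%. The stated rate implies 27.1% (1 - 0.729) or 30%.

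**Effect on the planned analysis.** Time at risk for the primary endpoint ends at TB, at loss or at three years. With constant TB rate r and loss rate h, the TB-free person-years per arm are n x [1 - exp(-3(r + h))] / (r + h).

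| Case | h | Arm at 7/100 | Arm at 3/100 | Expected TB events |
| --- | --- | --- | --- | --- |
| 250 per arm, no loss | 0 | 676 | 717 | 68.9 |
| 325 per arm, 27.1% lost by 3 years | -ln(0.9) = 0.105 | 758 | 801 | 77.1 |
| 325 per arm, 30% lost by 3 years | -ln(0.7)/3 = 0.119 | 744 | 786 | 75.7 |

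Events are 0.07 x the first arm's person-years plus 0.03 x the second's. In the second row, for example, 0.07 x 758.2 + 0.03 x 801.3 = 53.1 + 24.0 = 77.1.

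Approximate log-rank power (Schoenfeld) uses z = |ln(3/7)| x sqrt(D/4) - 1.96, where D is the number of events. Two-sided 5% is an assumption, because the section states no alpha.
- D = 68.9: 0.847 x 4.15 - 1.96 = 1.56, power about 94%.
- D = 77.1: 0.847 x 4.39 - 1.96 = 1.76, power about 96%.
- D = 75.7: 0.847 x 4.35 - 1.96 = 1.73, power about 96%.

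**The case against.** The strongest reply is that the planned analysis does not use the head-count at 36 months. The protocol never says that the 250 are completers, and it derives them from rates per person-year. In a person-year or log-rank analysis, patients who die or default contribute time until they leave. On that measure 325 with 10% annual loss supplies more than 250 patients followed fully, so the allowance is more than enough. This stands. It removes any claim of harm to the primary comparison, but it does not make 325 the result of the stated allowance.

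A second reply is that multiplication is only inferred. Another route reaches the same number: counting third-year losses as present for half of that year gives 250 / (0.9 x 0.9 x 0.95) = 324.9. That is the intake needed for an average of 250 under observation during year 3. Nothing in the protocol indicates that this was done, but it shows that the exact match with 250 x 1.30 does not prove how 325 was obtained. That also stands. The finding that 325 does not leave 250 at three years does not depend on the route; it follows from the stated rate and duration.

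**Conclusion.** The point holds as a minor arithmetic fault. At the stated loss, 325 per arm leaves about 237 or 228 at 36 months, which is 13 to 22 short of 250; retaining 250 would take 343 or 358. This rests only on the stated 250, the 10% annual rate and three years of follow-up.

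A reader might infer that the trial is underpowered or must enrol more patients. The documents do not support that. A fall in power appears only if patients who leave are discarded and completers are compared as proportions, which the protocol does not plan. Under the planned analysis the direction is the opposite, provided that 250 meant patients followed for the full three years: about 76 to 77 expected TB events against 69. The person-year, event and power figures further assume constant TB and loss rates, loss unrelated to TB risk, the two stated TB rates in the two arms and, for power, two-sided 5%.

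**What to change.** Keep 650 and restate the Sample Size section so that it says:
- 325 per arm, with 10% annual loss, leaves about 237 per arm under observation at 36 months (about 228 if the loss is 10% of the original number each year);
- whether 250 meant completers or person-time;
- that the size is justified by the expected person-years or TB events for the log-rank test, with the alpha and power used. On the protocol's rates these are about 758 and 801 TB-free person-years and about 77 events in total when 10% of those remaining leave each year.

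Person-years should be given separately for each arm, because TB ends time at risk and the assumed rates differ. If the sponsor did intend 250 completers per arm, the inflated number consistent with that is 343 or 358.

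If 650 is kept, the cost is wording only. Enrolment, conduct and analysis do not change.
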